### Recruitment

2.1

We will collect data from an ongoing multi-center randomized controlled trial examining the efficacy of a sTBI treatment strategy guided by both ICP and brain tissue oxygen (PbtO2) as compared to a strategy guided by ICP monitoring alone [Brain Oxygen Optimization in sTBI (BOOST), Phase 3, NCT03754114] (17). As part of the trial, the ECG waveform with four-leads and arterial blood pressure waveform data will be collected over the first 5 days of their intensive care unit (ICU) stay. Our ancillary study (AUTO-BOOST) will leverage this rich and granular waveform data to fully characterize autonomic dysfunction following sTBI.

We are sourcing data from this active clinical trial (BOOST), the trial has enrolled 550 patients. Since unexpected issues may arise during data collection, such as failures to collect data due to leads detaching or errors caused by device malfunctions, we estimate that approximately 50% of patients will have adequate cardiac telemetry data of sufficient quality for analysis. The Moberg monitor (CNS Monitor, Moberg ICU Solutions, Amber, Pennsylvania, United States) will capture and time-synchronize these analog data with other vital signs, ventilator data, and ICP/PbtO2 data, storing all data locally. A research team member will extract and upload the waveform data to a secure IBM cloud-based server. We will extract ABP, ECG data, and ventilator parameters from the Moberg device, deriving heart rate from the raw ECG tracing. We will use cleaned segments of stable recordings within 24 h of ICU admission for analysis.

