### Data analysis

2.2

Based on data from the currently recruited 550 patients, we found some incomplete ECG recordings of short duration, necessitating data analysis based solely on the ABP signal. To address this issue, we will conduct the eAD characterization on two fronts: one from both ECG and ABP waveforms, and the other from only ABP waveforms.

We will conduct non-invasive characterization of eAD by computing multiple indices over 24 h following admission, including heart rate turbulence (HRT) (18), time- and frequency-domain analyses of HRV and sequence analysis of BRS. First, we will slice the long-monitoring waveform into 1-h segments and assess the signal quality for both ECG and ABP segments. Next, the premature ventricular contractions (PVC) detection will analyze high-quality ECG segments. If more than 10 PVC beats for a given 1-h segment are detected, we will conduct HRT analysis on ECG waveforms (19). HRT is generally assessed by two parameters: turbulence onset (TO) and turbulence slope (TS). TO measures the initial acceleration and subsequent deceleration of heart rate after a PVC, while TS quantifies the rate of heart rate return to baseline. We will extract two time series from the ECG and ABP waveforms: one consisting of RR intervals from normal sinus beats, and the other comprising systolic blood pressures (sBP) from ABP pulses. We will then perform three analyses on these sequences: extracting root mean square of successive differences (RMSSD) and HRT from time-domain RR interval sequences, transforming RR intervals into the frequency domain to calculate the low- and high-frequency band ratio, and estimating BRS indices from RR intervals and sBP sequences. For eAD characterization based on ABP signals alone, we will compute autonomic indices from pulse interval sequences, excluding HRT due to the difficulty of detecting PVC beats without ECG waveforms. Figure 1 summarizes the entire procedure, with detailed explanations of each function block provided in the following sections.

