We will assess ABP signal quality using a singular value decomposition (SVD)-based approach (24). We will use our previously developed pulse detection algorithm to mark the onset of each ABP pulse, normalizing each pulse in both time and amplitude (25). Once the onsets of pulses are identified, we will adjust each pulse to a fixed length using spline resampling to ensure consistency in the number of data points across all pulses. Additionally, we will standardize each pulse’s amplitude by centering it around zero and scaling it to a standard deviation of one. Then, we will project this ABP pulse onto the signal subspace based on the SVD approach and calculate the signal-to-noise ratio. To obtain the signal and noise subspaces, we will implement SVD approach on an expert-validated reference library of 567 ABP pulses collected from 51 patients hospitalized at UCLA Ronald Reagan medical center. These valid ABP pulses will be subjected to the same normalization process. We will define the signal subspace and noise subspace after conducting SVD valid ABP pulses in the reference library. For a test ABP pulse, we will first project it onto the signal subspace and calculate the ratio of the energy of the projected signal over that of the projected noise. This ratio will be compared with a threshold, which is defined as the minimum calculated ratio among all the 567 pulses in the reference ABP library. This setting ensures that any ABP pulse closely resembling any pulse in the validated library is assessed correctly, providing a robust measure against false detections. The valid ABP pulses are those with calculated ratio greater than the threshold. We will conduct subsequent analysis only on the one-hour segments that pass both ECG and ABP signal quality assessments.

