For the case of eAD characterization utilizing ABP signal alone, we will extract pulse-to-pulse interval (PPI) based on detected systolic blood pressure from high-quality ABP waveforms and calculate pulse rate variability. We identify the intervals between fiducial points in successive pulses as PPI. Based on PPI time series, we will calculate RMSSD, the ratio of LF/HF and BRS metrics in place of using RR interval time series.

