### Coherence analysis

2.3

Coherence analysis between pulse rate variability and blood pressure variability will be performed on 1-h ABP waveform segments. Peaks corresponding to systolic pressure of each cardiac cycle will be detected, and Gaussian filter will be applied to exclude frequencies above 10 Hz (47). Pulse rate variability and blood pressure variability will be calculated based on frequency domain analyses of the waveform derived after applying a Gaussian shape to the time differences between subsequent cardiac cycles. Power spectral density (or power spectrum) will be used to quantify the frequency content of a blood pressure variability or pulse rate variability. Coherence will be calculated using mscohere function in MATLAB (47).

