## Discussion

5

This study’s novelty lies not in the development of new autonomic measures, but rather in three key aspects: (1) the first application of HRT analysis in sTBI patients, providing new insights into post-ectopic beat autonomic regulation in this population; (2) the comprehensive integration of multiple autonomic measures in a large cohort of sTBI patients, allowing for robust characterization of autonomic dysfunction patterns specific to this population; and (3) the potential to establish normative values and clinical thresholds for autonomic measures in acute sTBI, which are currently lacking. This approach will provide clinicians with a more complete understanding of autonomic dysfunction in sTBI and its relationship to clinical outcomes.

Following sTBI, eAD is a complex and multifaceted issue that can significantly impact a patient’s overall health and recovery. Characterizing eAD is crucial for risk assessment, customizing pharmacological interventions, and assessing rehabilitation strategies. While small studies indicate that eAD is associated with poor outcomes following sTBI, the duration and full trajectory of eAD has been poorly characterized. This protocol outlines the data analysis procedure for quantifying acute autonomic dysfunction using cardiac telemetry waveforms. We will collect and annotate waveform data from 550 patients in a clinical trial and quantify the incidence and magnitude of eAD indices after the first day of admission. We will characterize eAD as the presence of 3 or more indices less/greater than 2.5 SDs of age/sex-standardized values measured over 24 h following admission.

In some patients, simultaneous ECG and ABP signals may be unavailable. To solve this problem, we will divide the collected data into subgroups with and without ECG information and examine eAD within both subgroups. We will report results of the planned study in one or multiple scientific papers in international peer-reviewed journals. We will note and deviations from this protocol, if any occur, in these publications.

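### The quality rule admits only hours that pass both the ECG and the ABP check, which contradicts the planned ABP-only front and the ABP-based coherence analysis

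*Protocol article*

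**What the plan says.** All references are to the protocol article.

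- Section 2.2.1 (Signal quality assessment) describes the ECG and ABP checks and closes with: "We will conduct subsequent analysis only on the one-hour segments that pass both ECG and ABP signal quality assessments".
- Section 2.2 (Data analysis) sets out two fronts, "one from both ECG and ABP waveforms, and the other from only ABP waveforms". The reason given for the second is that "we found some incomplete ECG recordings of short duration, necessitating data analysis based solely on the ABP signal".
- Section 2.2.6 (Heart/pulse rate variability analysis) says of the ABP-only case: "we will extract pulse-to-pulse interval (PPI) based on detected systolic blood pressure from high-quality ABP waveforms". RMSSD, LF/HF and BRS then come from those pulse intervals. No ECG condition is attached.
- Section 2.3 says: "Coherence analysis between pulse rate variability and blood pressure variability will be performed on 1-h ABP waveform segments". Again there is no ECG condition.
- The Discussion (Section 5), on patients who lack simultaneous signals, says that "we will divide the collected data into subgroups with and without ECG information and examine eAD within both subgroups".

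Section 2.2 also passes ECG segments judged to be of good quality to PVC detection, without asking for good ABP in the same hour.

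**The concern.** The closing sentence of Section 2.2.1 comes before every analysis step and applies to whatever follows. The words for only and both make it a joint requirement with no carve-out. The second front exists to rescue recordings in which the ECG cannot be used, and a rule that requires a usable ECG shuts out exactly those recordings.

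At stake is whether one of the two planned characterizations can be carried out as described. Two programmers could also build different datasets from the same text. One would apply the rule everywhere and find no hours with failed ECG to analyse. The other would assume an unstated exception. The patients contributing to each front, and so the reported frequency of early autonomic dysfunction by front, would depend on which reading was taken.

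**Working it through.** The plan states no figure to reproduce here. The check is logical: compare what the rule admits with what each analysis needs.

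**Step 1. Classify each one-hour segment.** Let E = 1 if the ECG check is passed and 0 if ECG is missing or fails. Let A be the same for ABP. Section 2.2.1 keeps a segment only if E = 1 and A = 1.

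**Step 2. Set the rule against the input of each planned analysis.**

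| Analysis | Where described | Signal needed | Hours with E = 0, A = 1 kept by the rule |
|---|---|---|---|
| RMSSD, LF/HF and BRS from pulse intervals (ABP-only front) | 2.2, 2.2.6, 5 | ABP | 0 |
| Coherence of pulse rate and blood pressure variability | 2.3 | ABP | 0 |
| BRS from RR intervals and sBP | 2.2, 2.2.5 | ECG and ABP | not eligible in any case |
| HRT, RMSSD, LF and LF/HF from RR intervals | 2.2, 2.2.4, 2.2.6 | ECG | not eligible in any case |

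The ABP-only front was created for hours with E = 0 and A = 1. The rule requires E = 1. The two conditions exclude each other, so the number of such hours kept is 0. This needs no assumption about how often either signal passes.

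**Step 3. Look for an exception.** Sections 2.2, 2.2.6, 2.3 and the Discussion describe ABP-only work without an ECG condition, but none of them says that the joint rule is lifted. Section 2.2.1 does not say that it applies to one front only.

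**Step 4. The ECG side.** Section 4 lists five indices: RMSSD, HRT, BRS, LF power and LF/HF. Four of them (5 − 1 = 4) need only RR intervals; BRS alone also needs sBP. As 4 is at least 3, the threshold of three abnormal indices could in principle be reached from ECG alone. The joint rule drops every hour with E = 1 and A = 0. That sits awkwardly with the unconditional routing of good ECG segments to PVC detection in Section 2.2. It is not a contradiction of the same kind, because Section 2.2 defines the first front as using both waveforms and plans no ECG-only front.

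**The case against.** The strongest reply is that the plan describes the ABP-only front in specific terms three times: with its reason in Section 2.2, its input in Section 2.2.6 and its subgroup in the Discussion. An analyst who reads these together would probably take the sentence in Section 2.2.1 to govern the combined front only. Figure 1, said to summarize the procedure, was not available for this review and may show separate checks. This stands as an account of the likely intention, and it means that an empty ABP-only front is what the rule yields literally, not a forecast of what the authors will report. It does not remove the contradiction. If Figure 1 shows separate checks, Section 2.2.1 disagrees with it and still needs correcting.

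Three stronger readings are tempting and are not supported.

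- *A reader might infer that dropping hours with good ECG and failed ABP is also an error.* Requiring both signals in the combined front may be deliberate, since it takes BRS and the ECG-derived indices from the same hours. Choosing the hours index by index has costs: indices would come from different hours, and a patient without BRS would have four indices against a rule written for five.
- *A reader might infer that the plan misstates its denominator.* Section 2.1 says "we estimate that approximately 50% of patients will have adequate cardiac telemetry data of sufficient quality for analysis", while the Discussion says "We will collect and annotate waveform data from 550 patients in a clinical trial". The second is a statement about collection and is compatible with the first. Nothing names 550 as the denominator for incidence, and no precision is claimed.
- *A reader might want the share of hours lost.* The document gives no pass rate for either signal. Section 2.2.1 names body motion among the noise sources for both waveforms, so independence of the two checks cannot be taken for granted. The expected 50% refers to patients and is not split by signal, so it cannot size the loss.

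**Conclusion.** The rule is wrong as written. Applied literally, the closing sentence of Section 2.2.1 leaves the ABP-only front with none of the hours that have missing or failed ECG, and removes the same hours from the coherence analysis. That zero follows from the wording alone and rests only on the premise that an hour without acceptable ECG cannot pass the ECG check. How many hours or patients this concerns cannot be derived from the document. The defect is one of scope in a single sentence, and the authors' intention is fairly clear from the other sections. The handling of hours with good ECG and failed ABP is a design choice to be stated, not an error.

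**What to change.** **Required.** Reword the last sentence of Section 2.2.1 so that the joint requirement applies to the combined ECG and ABP front, or at the least to BRS computed from RR intervals and sBP. Add that the pulse-interval indices of the ABP-only front and the coherence analysis in Section 2.3 use segments that pass the ABP check alone. Check that Figure 1 shows the same rules. The cost is one or two sentences; no new data are needed.

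**Optional.** The authors could also use hours with good ECG and failed ABP for HRT, RMSSD, LF power and LF/HF. They would then need to state how the rule of three out of five indices works when BRS is unavailable, and to accept that a patient's indices may come from different hours. This costs some programming and one further definition. If they prefer to keep both signals as a condition of the combined front, a sentence saying that this is intended is enough, with the routing of ECG segments to PVC detection in Section 2.2 worded to match.

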#### Peaks detection

2.2.2

We will recognize R peaks for each ECG beat using a published QRS detection algorithm that includes four steps (26). The first step will use a sliding window of 2 s to capture the ECG signal. In the second step, we apply a band-pass filter ranging from 0.5 to 17 Hz to eliminate signal noise and motion artifacts. Then, we apply an enhancement mask to the filtered signal as Equation 4:

(4)
$$S\left(n\right)=\overset{k}{\underset{j=-k}{\sum }}M\left(k+j\right)E\left(n+j\right)$$

The enhancement mask 
M
 is defined as Equation 5:

(5)
$$\left\{\begin{array}{c} M\left(n\right)=-1,n\in \left[0,k-1\right]\\ M\left(n\right)=2*k,n=k\\ M\left(n\right)=-1,n\in \left[k+1,2k\right] \end{array}\right.$$

where 
E
 is the filtered ECG signal and 
S
 is the enhanced ECG signal. To eliminate variations in QRS amplitude, we will normalize the amplitude of the enhanced ECG signal to 1 using min-max normalization.

The third step is the detection of QRS fiducial points based on detected crests and troughs. Based on the normal range of the QRS complex in a typical lead-II ECG waveform, as shown in a published work, we will use a searching range of 0.3 s to detect the QRS complex. The searching process starts at the first point of the normalized ECG signal, and the amplitude threshold for detecting the QRS complex will be defined as 0.5 mV (26). The last step is the R peak recognition based on the detected QRS fiducial point. Since a normal QRS rangs is less than 0.12 s, the time interval for recognizing R peak is set as 0.24 s centering at the fiducial point in (26), and we identify the R peak successively.

For the high-quality ABP waveform, we will detect systolic blood pressure based on a published algorithm (27). Initially, we will apply a Savitzky–Golay filter to remove noise. Subsequently, we will utilize a sliding window to correctly identify the maximum point of the arterial pulse.

#### PVC detection

2.2.3

Because HRT that occurs after a premature ventricular contraction (PVC) can reflect the condition of the autonomic nervous system (28), detection of PVC beats is for subsequent HRT calculation. To reduce the computation cost, we will primarily classify ECG signals into PVC or non-PVC segments and then detect PVC locations only on PVC segments.

We will first classify 1-h ECG signals into PVC or non-PVC segments using an existing algorithm, which employs a Siamese network architecture to capture complementary information from two-lead ECG signals (29). During training, the model will take a pair of ECG signals as inputs. In each training iteration, the two signal modalities will take turns flowing through the encoder and the projector of this network. The learned features of one ECG channel will pass through the predictor to map to the latent space of features from the other ECG channel. We will optimize an agreement loss between the predicted latent feature vector of one ECG channel ECG and the projected latent feature vector of the other ECG channel. We will also optimize a supervised cross-entropy loss for the output of the classifier function, which takes the latent features of one ECG channel as inputs. Upon completion of training, only the encoder and classifier are preserved for subsequent predictions. During testing, the trained network can operate using single lead ECG independently, without necessitating an ECG signal pair. After the PVC segments are classified, we will adopt the algorithm in (30) to identify the PVC locations in two stages. In the first stage, based on the PVC morphological characteristics in high width, large amplitude and an abnormal waveform, we identify rough PVC beats through the quantification of these qualities with rules. In the second stage, we refine detection to reject false positive and normal beats. If a solitary PVC candidate is identified after initial screening and its morphology closely aligns with that of the majority of other beats, it should be reclassified as non-PVC and excluded from further consideration. Conversely, if there are multiple PVC candidates, their widths (cW) are computed at three-fourths the height of the smallest candidate. Subsequently, the PVCs are assessed pairwise. A PVC that exhibits considerable deviation from others and possesses a cW exceeding the mean is designated as an ectopic PVC. Candidates failing to meet these criteria are categorized as non-PVC and consequently excluded from the analysis.

##### Methods evaluation

2.2.3.1

PVC detection enables the correct identification of HRT onset and slope. To obtain the accurate location of PVCs, we will test several PVC detectors, including the Siamese network-based PVC algorithm mentioned above, using publicly available datasets and compare their performance. We will select the method that demonstrates optimal performance as the final solution for PVC detection on our collected waveform data. The evaluation process will include the following steps.

###### Evaluation dataset

2.2.3.1.1

We will use the St Petersburg INCART 12-lead Arrhythmia database available from Physionet (31) as the evaluation dataset. This database includes multiple recordings from each of the 32 patients undergoing tests for coronary artery disease, resulting in 75 annotated recordings (17 men and 15 women, aged 18–80; mean age: 58). In selecting records for inclusion, preference was given to subjects with ECGs indicative of ischemia, coronary artery disease, conduction abnormalities, and arrhythmias. Each recording is 30 min and sampled at 257 Hz. The PVC beat is annotated by an automatic algorithm and manual correction. Because PVC is global and training model can learn from more exposures to different combinations of ECG leads, we will expand the training dataset by forming more pairs of ECG leads. Then, we will slice the ECG signals into 30 s segments with 1 s nonoverlapping. We label each 30 s segment as a PVC segment if it contains at least one PVC beat. We then apply the five-fold cross-validation splitting data based on subjects to validate the performance of the algorithm. We will use the MIT-BIH Arrhythmia database available from PhysioNet (31, 32) as the test dataset, which includes 48 2-lead ECG recordings obtained from 47 subjects (two recordings from the same subject), studied by the BIH Arrhythmia Laboratory. The subjects include 25 men aged 32 to 89 years and 22 women aged 23 to 89 years.

###### Evaluation with state of the art PVC detections

2.2.3.1.2

Several state-of-the-art tools for PVC detection are available with open code, and we will compare them to our primary method. The first one proposes a convolutional neural network-based deep learning model, ECGDet, to detect PVC beats for every 32 points of the ECG signals (33). The second PVC detection algorithm involved two stages (34): the first classifies heartbeats into ectopic and non-ectopic beats, and the second further classifies the ectopic heartbeats into PVC beats. The last algorithm (35) combined the long short-term memory network with autoencoder to extract features of ECG heartbeats for K-means clustering and construct templates. This algorithm identifies PVC beats based on the similarity with these templates. To evaluate the performance of PVC detection, we will use sensitivity (Sen), specificity (Spec), accuracy (Acc) and F1-score. The definitions of these four metrics are provided in the Appendix.

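### As described, the PVC detector comparison fixes no common counting unit and does not clearly test PVC location, which heart rate turbulence depends on

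*Protocol article*

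**What the plan says.** Section 2.2.3 (PVC detection) describes a two-step primary method. A Siamese network first classifies ECG segments as PVC or non-PVC, to save computation. A separate rule-based algorithm (reference 30) then finds the PVCs within the positive segments.

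Section 2.2.3.1 (Methods evaluation) gives the purpose of the comparison: "To obtain the accurate location of PVCs, we will test several PVC detectors, including the Siamese network-based PVC algorithm mentioned above". It also gives the selection rule: "We will select the method that demonstrates optimal performance as the final solution for PVC detection on our collected waveform data". No deciding metric is named.

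Section 2.2.3.1.1 (Evaluation dataset) defines the reference label on the INCART data: "We label each 30 s segment as a PVC segment if it contains at least one PVC beat". The validation scheme follows directly: "We then apply the five-fold cross-validation splitting data based on subjects to validate the performance of the algorithm". The same section says that PVC beats are annotated in INCART, and it names MIT-BIH as the test set without stating a label or unit for it.

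Section 2.2.3.1.2 lists three comparators. One is a network said "to detect PVC beats for every 32 points of the ECG signals", one classifies heartbeats in two stages, and one matches beats to templates. For all methods: "To evaluate the performance of PVC detection, we will use sensitivity (Sen), specificity (Spec), accuracy (Acc) and F1-score". The Appendix defines sensitivity and specificity in terms of PVCs and non-PVCs, and accuracy over a number of instances that is not defined further.

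**The concern.** The purpose is location, but a 30-second any-PVC label says nothing about where in the 30 seconds a PVC lies or how many there are. The step that produces location for the primary method is not named among the things to be tested. If the Siamese network is scored on segments and the comparators on beats, the four metrics carry the same names but count different things, and the best performer is not well defined.

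The selected detector feeds section 2.2.4. Heart rate turbulence is computed only when more than 10 PVC beats are detected. Turbulence onset (TO) and slope (TS) use RR intervals indexed to each PVC's coupling and compensatory intervals, and both are averaged over all detected PVCs. A missed PVC can take an hour below the threshold, and a misplaced or false one puts the wrong intervals into the averages. The Discussion lists the first use of this analysis in severe TBI as the first of its three novel aspects, so the choice of detector matters to the study's own claims.

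**Working it through.** The protocol gives no detector performance figure, so there is none to reproduce. The check has two parts: set the units side by side, then illustrate what a change of unit does.

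**1. Units as described**

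| Element | Unit | Place |
|---|---|---|
| Purpose of the comparison | PVC location | 2.2.3.1 |
| Reference label | 30-s segment, any PVC | 2.2.3.1.1 |
| Siamese network output | segment class | 2.2.3 |
| Localiser (reference 30) | beat | 2.2.3; not named in 2.2.3.1 to 2.2.3.1.2 |
| Three comparators | beat | 2.2.3.1.2 |
| Sensitivity, specificity | PVCs, non-PVCs | Appendix |
| Accuracy | instances, undefined | Appendix |
| Use of the result | individual PVC beats | 2.2.4 |

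The segment label is the only reference label defined, and it fits neither the comparators' output nor the use.

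**2. Effect of the unit on one detector**

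Assumptions, none from the protocol: beat sensitivity s, beat specificity c, PVC share of beats p, n = 40 beats per 30 s (80 per minute), independent errors.

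- Probability that at least one of k PVCs in a segment is found = 1 − (1 − s)^k. With s = 0.70 this is 0.70, 0.91, 0.973 and 0.998 for k = 1, 2, 3 and 5.
- Segment specificity = c^n. With c = 0.99, 0.995 and 0.999 this is 0.669, 0.818 and 0.961.

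So aggregation to segments tends to raise sensitivity and lower specificity.

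Detector A: s = 0.70, c = 0.995, p = 0.02.

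- Beats: TP = 0.02 × 0.70 = 0.0140; FN = 0.0060; FP = 0.98 × 0.005 = 0.0049; TN = 0.98 × 0.995 = 0.9751. F1 = 0.0280 / (0.0280 + 0.0049 + 0.0060) = 0.720. Accuracy = 0.0140 + 0.9751 = 0.989.
- Segments: P(no PVC) = 0.98^40 = 0.446. TN = 0.9751^40 = 0.365. FP = 0.446 − 0.365 = 0.081. P(no flag) = (0.0060 + 0.9751)^40 = 0.466, so FN = 0.466 − 0.365 = 0.101. TP = 1 − 0.446 − 0.101 = 0.453. Sensitivity = 0.453 / 0.554 = 0.817. F1 = 0.906 / (0.906 + 0.081 + 0.101) = 0.832. Accuracy = 0.453 + 0.365 = 0.818.
- With p = 0.10 the same steps give F1 of 0.802 on beats and 0.982 on segments.

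**3. Effect on a ranking with mixed units**

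Detector B: s = 0.90, c = 0.99, p = 0.02, scored on beats. TP = 0.0180; FN = 0.0020; FP = 0.98 × 0.01 = 0.0098; F1 = 0.0360 / 0.0478 = 0.753. Accuracy = 0.0180 + 0.9702 = 0.988.

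- F1, both on beats: B leads, 0.753 to 0.720.
- F1, A on segments and B on beats: A leads, 0.832 to 0.753.
- Accuracy, A on segments and B on beats: B leads, 0.988 to 0.818.

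The winner depends on the unit and on which of the four metrics decides, and the protocol fixes neither.

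**4. What heart rate turbulence would receive**

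In the p = 0.02 case, detector A misses 30% of PVCs. Of the beats it flags, 0.0049 / (0.0140 + 0.0049) = 26% are not PVCs. A segment F1 of 0.83 shows neither figure.

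**The case against.** The strongest case on the other side is that a beat-level comparison may be what is meant. The Appendix words sensitivity in terms of PVCs found and never mentions segments. The segment label appears alongside the text on building training pairs, and the cross-validation is of one algorithm, so the label may belong only to developing the pre-screen. MIT-BIH carries no segment label in the text. No sentence says that the comparators are scored on segments, and testing the whole chain would fit the stated purpose.

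This stands in part. A reader might infer that the comparison certainly fails to test location; the documents do not go that far. They do leave the segment as the only defined label, the localiser unnamed and the counting unit open, in a text that otherwise sets out the datasets, metrics and selection rule.

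A reader might also infer that segment scoring flatters the primary method. That is not shown. Aggregation lowers specificity while it raises sensitivity, and the Siamese network classifies segments directly, so it has no beat sensitivity of its own to aggregate. The assumed performance values have no support in the protocol, and misses may cluster within a patient with one PVC morphology, which would shrink the gain in sensitivity.

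Finally, a reader might infer that detector errors spread to RMSSD, LF/HF and baroreflex sensitivity through the RR series, which is restricted to normal sinus beats. This is plausible, but section 2.2.3 ties PVC detection to heart rate turbulence only. Whether MIT-BIH is reused for both selection and reporting is a separate question that this evidence does not establish.

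**Conclusion.** The point holds as a defect in how the comparison is described. Its purpose is PVC location, its only defined label carries no location, the primary method's localiser is not named for testing, and the methods have no stated common unit. The ranking may therefore select a detector that misses or misplaces PVC beats.

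The size cannot be derived from the protocol. The gap between F1 of 0.72 and 0.83 (0.80 and 0.98 at 10% PVC beats) and the change of ranking show only that the two units are not comparable. They rest on assumed beat performance, 40 beats per segment and independent errors, and do not predict how the Siamese network will perform.

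The reach is limited. It concerns mainly TO, TS and the threshold of more than 10 PVCs. Heart rate turbulence is one of five indices, and early autonomic dysfunction needs at least three. An error in this index therefore changes a patient's classification only when exactly two of the other four are abnormal.

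**What to change.** - Keep the 30-second label for training and validating the segment pre-screen, and say that this is its only use.
- Select the final detector by scoring every method beat by beat against the annotated PVC beats, with one stated matching tolerance.
- Score the Siamese network after its localiser, so that the chain to be used on the trial data is the one tested.
- Name one beat-level selection metric in advance, for example F1, and define the Appendix's instances as beats for this comparison.

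INCART already carries PVC beat annotations, so no new labelling is needed there. The cost is a modest amount of rescoring and a few sentences in sections 2.2.3.1 to 2.2.3.1.2 and the Appendix.
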